## Abstract

**Background:**

Past research has identified links between intimate partner violence (IPV) and alcohol misuse and poverty in Sri Lanka. Services that address substance misuse are amongst the few interventions shown to reduce IPV in settings similar to Sri Lanka. This paper describes the protocol for a study examining the impact of a preschool-based capacity building intervention on the prevalence of IPV and substance misuse in parents with children attending preschools, including uptake of available government services.

**Methods:**

The study is a cluster randomised controlled trial. Government-managed preschools (*n* = 34) in Galle and Colombo municipalities  will be randomly assigned to an intervention (*n* = 17) or control group (*n* = 17). Parents with children attending these preschools will be recruited to participate. The study intervention will build the capacity of selected community volunteers (parents) and preschool teachers in the provision of information and support to families affected by IPV and substance misuse. This intervention is directed at improving uptake, access and coordination of existing services. Data will be collected from all parents, and teachers in the intervention group, pre-intervention and 10 months post-intervention. The primary outcome for this study is experience of IPV amongst mothers of preschool-attending children. Secondary outcomes are substance misuse amongst fathers, measured via the locally adapted Alcohol Use Disorders Identification Test and Drug Abuse Screening Test; and awareness and uptake of services for these issues measured through locally-relevant tools. Demographic information and satisfaction with the intervention will also be assessed.

**Discussion:**

By intervening through preschools we aim to support high-risk families early enough to arrest the cycle of violence that results in children themselves becoming victims and perpetrators of such violence. The innovative project design will reach the most vulnerable sections of the community and will provide a sustainable and feasible strategy for scale-up of the intervention.

**Trial registration:**

This study is registered with the Sri Lankan Clinical Trials Registry (2017/038) and has been submitted to ClinicalTrials.gov (U.S National Institutes of Health) under the title “Randomized control trial: preschool-based training and support programs to reduce intimate partner violence (IPV) by addressing alcohol and drug misuse in young families in Sri Lanka”; Registration number: NCT03341455; Registration date: 14 November 2017.

## Background

Past research has identified that intimate partner violence (IPV) in Sri Lanka is often associated with poverty and alcohol misuse [1]. Such violence is linked to high levels of psychological distress among children [2, 3], and childhood experience of IPV is also a strong predictor of experiencing or using violence as an adult [1]. Drug misuse is an increasing problem in Sri Lanka [1] and is also likely to contribute to IPV. Ensuring that those affected by IPV or substance (drug and alcohol) misuse receive support is critical in improving long-term outcomes. Of particular importance is ensuring that this support is received early enough to disrupt the inter-generational cycle of violence that can result from childhood exposure to these risks.

Services that address alcohol misuse by perpetrators of domestic violence are amongst the few interventions shown to reduce IPV in settings similar to Sri Lanka [4, 5]. Services for addressing IPV and substance misuse in Sri Lanka are provided through both government and non-governmental agencies [6], but formal, integrated IPV and substance misuse programs do not exist. Uptake of services by those experiencing IPV is low, limited by factors including lack of awareness, poverty, stigma and limited coordination between different referral sectors. Interventions that improve the coordinated uptake of available services for IPV and substance misuse in Sri Lanka are needed and have the potential to not only improve substance use problems, but also to impact positively on prevalence of IPV.

Evidence, including from Sri Lanka, suggests that women suffering from IPV are more likely to seek support from family and community members in preference to formal support agencies [3, 7]. There is also evidence from high income settings that lay community members can be trained to effectively support those experiencing IPV to access services [8].

Preschool teachers and volunteer mothers and fathers (from the intervention group) will be trained as lay community members to support young families experiencing IPV or substance misuse. They will receive training on the impacts of parental IPV and substance misuse on children’s educational achievements, key messages to convey to families experiencing IPV or substance misuse, and practical information and resources for accessing services to assist families including contact details, referral criteria, duration of available programs, expected commitment of participant, costs of services and likely impact or benefit of accessing the available services.

Preschools offer a route through which to implement community support programs to increase awareness, knowledge and uptake of services for IPV and substance misuse, and to target such programs to families with young children. Additionally, the preschool setting provides a route for delivering preventive messages in relation to these issues. The primary aim of the study is to determine whether such preschool-based capacity building programs reduce the prevalence of IPV in preschool-attending families. Secondary aims include assessing the impact of such programs on awareness and uptake of services, and on prevalence of alcohol and drug misuse in these families.

## Methods

We hypothesise that building the capacity of selected parents and preschool teachers in the provision of information and support for accessing appropriate government services to young families attending preschools who may be affected by IPV and substance misuse will have positive effects on:Prevalence of IPV reported by women in the intervention groupPrevalence of drug and alcohol misuse reported by men in the intervention groupAwareness and uptake of available government services that address these issues  by young families

We will address the hypothesis using a randomised controlled trial (RCT) to deliver and evaluate a community-based advocacy intervention that is affordable, adaptable, effective, and community driven.

### Study design

The study is a preschool-based parallel group cluster RCT that will be conducted to assess the impact of a capacity building intervention on IPV and alcohol and drug misuse related knowledge, practices and prevalence. The comparison is between preschools who receive targeted training (intervention group) and the preschools that do not (control group). Parents with children attending government-managed preschools in two study areas will be recruited to participate. Conventional RCTs, in which individuals are randomly allocated to different treatment groups, are inappropriate for interventions where the level of allocation is a cluster, based around a health facility, village or preschool as is the case in this study. Figure 1 provides an overview of the study design.

**Fig. 1 Fig1:**
[figure not shown]
Study design and timeline

### Setting

Preschools in Sri Lanka are attended by children aged between 3 and 5 years for at least one year prior to starting school and coverage in this age group is estimated at 46% [9]. The majority of preschools are privately run. Although government-run preschools constitute only 16% of all preschools [9] they are free of charge and are generally most utilised by economically disadvantaged sections of the community.

Education is highly valued in Sri Lanka, even amongst the most socio-economically disadvantaged, and parents will invest significant resources in ensuring the educational success of their children. Based on discussions with preschool teachers and community service providers (both government and non-government) we assert that explicitly linking IPV and substance misuse to poorer educational outcomes for children will support prevention of these issues, as well as provide motivation to those parents affected by these issues to seek assistance. By ensuring information on such assistance is accessible through trusted community members, we hope to improve uptake, retention and post-treatment effectiveness of support services.

Our intervention will build the capacity of preschool teachers in providing preventive educational messaging, selected mothers in the provision of information and support for accessing services for IPV, and selected fathers in the provision of information and support for accessing services for substance misuse support services. By delivering these interventions through government preschools, we aim to deliver an intervention that targets poorer families with young children that is effective, feasible and sustainable within existing government and community resources and infrastructure.

### Target population

Our target population is families utilising government preschools in two urban areas in Sri Lanka: Galle urban municipality (Galle) and Dehiwala Mt Lavinia municipality (Colombo). The urban site in Galle covers 20 government-run preschools and Colombo covers 14. All parents of children attending these preschools will be eligible for inclusion in the study, and will be included if consenting.

### Recruitment

All parents from participating preschools will be invited to participate in the study. This invitation will be in the form of a written letter and verbal announcement made by the project intervention team. The parents who volunteer to participate will be invited to attend the school after-hours on a designated day to receive additional information and complete the baseline survey under the supervision of the data collection team. Mothers and fathers will be asked to attend on separate days. Two sessions (a weekday and a weekend session) will be offered to each group to allow participants a choice in the time at which they undertake the survey.

Participation is voluntary and any participant can leave the study at any time they wish. If a participant does leave during the duration of the intervention, any data provided by them up to that point will remain part of the study. Only de-identified data are collected. Therefore, the data collection team and data entry officer are unable to identify any participants who remain or withdraw from the study based on the information received.

In the randomly selected preschools that will receive the intervention, all mothers and fathers will be invited to volunteer to receive capacity building and training as part of the intervention. We aim to recruit two mothers and two fathers participating in initial workshops from each preschool. Those who volunteer will be interviewed by the training team (which is distinct from the data collection team) and selected based on their performance in an initial workshop. Mothers and fathers will attend separate workshops on different days. Training will be delivered to mothers and fathers separately on different days.

All teachers from participating preschools will be invited to attend the teacher training and will be included if they consent. All teachers, 10 randomly selected mothers and 10 randomly selected fathers who participated in the training, will be interviewed at the conclusion of the study.

### Randomisation

Randomisation will be at the level of the preschool stratified by study area. Half the preschools in each study area will be randomly allocated to receive the teacher and parent training intervention at the beginning of the preschool year (*n* = 17: 10 preschools in Galle and 7 in Colombo). The preschools that do not receive the intervention (*n* = 17: 10 preschools in Galle and 7 in Colombo) will act as time-concurrent controls. If the intervention is demonstrated as being effective, these control preschools will receive the intervention at the conclusion of the study.

Randomisation will be carried out by the study statistician based outside the study areas, blinded to study area and preschool, in a 1:1 ratio to intervention or control group stratified by study area and using a computer generated randomisation process. The allocation program will be archived for reproducible research compliance.

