### Data collection

Data from parents will be collected in de-identified form through anonymous, self-administered surveys. Literacy rates in Sri Lanka are very high for both men and women, so we do not expect illiteracy to be a barrier to participation. Data collection will be supervised by staff recruited specifically for this task. These staff will receive training prior to commencement of the baseline data collection which address the contents of the survey and how to provide confidential, safe and appropriate support to participants who seek or request assistance, including for domestic violence or substance misuse, during completion of the survey. Refresher training will be provided to the same team prior to the collection of post intervention data.

All government preschools in the study areas will be involved in the following data collection activities:A baseline survey of mothers and fathers at the beginning of the preschool year (January 2018)A follow up survey of all mothers and fathers at the end of the preschool year (December 2018).

Preschools receiving the intervention will participate in the following additional post intervention data collection activities:Qualitative interviews with key participants including teachers, community members, community development staff and other government sector service providers to determine their satisfaction with the intervention, and any challenges or barriers to its implementation.

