#### Sample size

The sample size was calculated to demonstrate a significant difference in the proportion of mothers of preschool children reporting exposure to IPV following intervention. We plan to recruit at least 34 preschools, with 20 families per preschool, for a total of 680 potential families (which equates to 340 families in the intervention group and 340 in the control group who may be approached to participate in this study. We anticipate minimal loss to drop out due to the educational focus on children this study promotes.

We assumed a participation rate of 90%, based on past research which found a consent rate in this population for domestic-violence related surveys of 97% [3]. We therefore expect a sample size of approximately 612 families, or 306 per group. Based on a design effect due to correlation of outcomes within preschools of 1.5 (which equates to an intra-class correlation coefficient of 0.025), 80% power, a 5% significance level and a pre-intervention 12 month prevalence of IPV of 40% [3] we will be able to detect a difference in post intervention 12 month prevalence of IPV between intervention and control groups of 15%.

There are no intervention studies in Sri Lanka or that region that examine the effects of community-based interventions. However, an extensive community-based intervention (SASA!) in Uganda, Africa reported a 53% reduction in physical IPV reported by women in the intervention group [17]. Therefore, we consider it justifiable to expect an intervention effect of at least 15%.

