#### Data analysis

The main analysis will be by intention-to-treat. The primary analysis will be a regression model of IPV experienced by mothers within the past 10 months in the intervention group, adjusted for other potential confounders, and correlation of outcomes within preschools using a Generalised Estimating Equations approach. Primary analysis will be a complete case analysis.

Similar analysis will be conducted for secondary outcomes including prevalence of substance misuse in fathers and awareness and uptake of services for IPV and substance misuse. Secondary analysis will use multiple imputation. Sensitivity analysis will be conducted through secondary adjusted analysis accounting for potential confounders. Confounders specified a priori as being potentially associated with the outcome include age, mental health status and socio-economic status.

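### The primary model names neither the randomisation stratum nor the baseline IPV survey, an efficiency and chance-imbalance weakness that preschool-level baseline data could repair

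*Protocol article*

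**What the plan says.** All references are to the protocol article.

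- **Randomisation:** "Randomisation will be at the level of the preschool stratified by study area". Target population gives 20 preschools in Galle and 14 in Colombo. Allocation is half and half within each area.
- **Data collection:** all preschools take part in "A baseline survey of mothers and fathers at the beginning of the preschool year (January 2018") and again in December 2018. Capacity building intervention places the training after the baseline survey and randomisation.
- **Outcome measures:** the contrast of interest is the difference between groups at follow-up.
- **Data analysis:** the primary analysis is a regression of IPV in the past 10 months, using GEE for correlation within preschools and adjusting for further possible confounders. The ones named are these: "Confounders specified a priori as being potentially associated with the outcome include age, mental health status and socio-economic status". Study area does not appear in this section, and neither does baseline IPV.
- **Recruitment** and **Ethical considerations:** surveys are anonymous, and answers cannot be tied to an individual within a preschool.
- **Conclusion:** the evaluation is described as resting on repeated cross-sectional surveys.

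**The concern.** Stratifying by area guarantees that the arms are balanced on area. Any real difference in IPV between Galle and Colombo therefore drops out of the arm comparison. A model without an area term does not recognise this: the area difference stays in the residual variation between preschools and inflates the standard error. The test then rejects too rarely under the null and loses power.

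The January survey is the only pre-intervention measure of the outcome. With 17 preschools per arm, the arms can differ noticeably at baseline by chance, and the model as stated has no term for that. Because the survey precedes training, the covariate cannot be affected by the intervention. Anonymity prevents adjustment for a mother's own baseline answer, but not adjustment for her preschool's baseline prevalence. At stake are precision from data already being collected, and a pre-specified answer if baseline prevalences turn out unequal.

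**Working it through.** **Inputs from the Sample size section.** Control prevalence 40%, difference 15 points, power 80%, significance level 5% (taken as two-sided). "We therefore expect a sample size of approximately 612 families, or 306 per group", which is 306/17 = 18 per preschool. "Based on a design effect due to correlation of outcomes within preschools of 1.5 (which equates to an intra-class correlation coefficient of 0.025"). I keep the design effect at 1.5 throughout, so the effective size is 306/1.5 = 204 per arm. At 18 per preschool, 1.5 corresponds to ICC = 0.5/17 = 0.0294. (The quoted pair, 1.5 and 0.025, fits 21 per preschool; 18 at 0.025 would give 1.425.)

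**Step 1: the plan's own figure.** Two proportions with pooled variance, 40% v 25%, mean 32.5%:

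n = [1.96·√(2·0.325·0.675) + 0.8416·√(0.24 + 0.1875)]² / 0.15² = 152 per arm, and 152 × 1.5 = 228.

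With 306 per arm, power for 15 points is 90% (89% on 32 degrees of freedom), and the difference detectable at 80% power is 13.05 points. The stated 15 points is therefore conservative; it fits 90% power (304.5 per arm). The starting point below is 13.1.

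**Step 2: preschool baseline prevalence as a covariate.** The correlation between a preschool's January and December prevalence is

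r = [m·ICC·CAC + (1 − ICC)·IAC] / [1 + (m − 1)·ICC],

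where CAC is the persistence of the preschool effect and IAC the persistence of a mother's own status. Here m·ICC = 0.529, 1 − ICC = 0.971 and the denominator is 1.5. The variance is multiplied by 1 − r². **CAC and IAC are assumptions; the documents give neither.**

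| CAC | IAC | r | Variance × | Detectable difference (points) |
|---|---|---|---|---|
| none (unadjusted) | – | – | 1 | 13.05 |
| 0.5 | 0 | 0.18 | 0.97 | 12.9 |
| 0.8 | 0 | 0.28 | 0.92 | 12.5 |
| 1.0 | 0 | 0.35 | 0.88 | 12.3 |
| 0.8 | 0.3 | 0.48 | 0.77 | 11.5 |
| 0.8 | 0.5 | 0.61 | 0.63 | 10.5 |

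Example (fourth assumed row): (0.529 × 0.8 + 0.971 × 0.3)/1.5 = 0.715/1.5 = 0.48. The rows with IAC above 0 need largely the same mothers to answer both surveys.

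These are gross gains. Estimating a slope from 34 preschools costs roughly 3% in variance. That cancels the first assumed row (0.97 × 1.03 ≈ 1.00) and leaves the second at about 0.95.

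**Step 3: the stratum term.** The area gap D is also assumed. It adds (20/34)(14/34)·D² to the variance of preschool prevalences when area is not modelled. The within-area variance of a preschool prevalence is 0.24 × 1.5/18 = 0.0200 in control and 0.1875 × 1.5/18 = 0.0156 in intervention.

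- D = 0: SE = √[(0.0200 + 0.0156)/17] = 0.046.
- D = 10 points: 0.0024 is added per arm, so SE = √[(0.0356 + 0.0048)/17] = 0.049.
- D = 20 points: 0.0097 is added per arm, so SE = √[(0.0356 + 0.0194)/17] = 0.057.

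With the stratum in the model, SE returns to about 0.046 in each case. A simulation of 34 preschool prevalences (2,000 runs per scenario) agrees:

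| Assumed gap | Power for 15 points, without → with area | Type I error without area |
|---|---|---|
| 0 | about 87% → 87% | about 5% |
| 10 points | about 84% → 87% | about 4% |
| 20 points | about 75% → 88% | about 2% |

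With area and baseline together, power was about 89% to 98% over the scenarios run.

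**Scale.** These are linear approximations on preschool means and the risk-difference scale. Data analysis names no link function. Under a logit link, adjustment also changes the odds ratio being estimated, and the factor 1 − r² does not carry over directly.

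**The case against.** **The covariate list is open.** A reader might infer that the plan limits adjustment to the three named covariates, or excludes area and baseline. It does not. Data analysis leaves room for other confounders, the quoted sentence says "include" rather than "only", and a fuller analysis plan, not shown, could add both terms. This stands, and the accurate statement is that the article does not name them. It does not dispose of the point. The article states a primary model and an a priori list, and following them as written leaves out the variable on which the allocation was stratified and the only pre-intervention measure of the outcome.

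**The baseline may be meant to have a role.** The Conclusion's repeated cross-sectional surveys are compatible with using both rounds. But Outcome measures and Data analysis give the January round no function in the comparison, and adjusting for it would not change the follow-up contrast.

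**The gain is assumed and may be nil.** This stands. If the areas do not differ and preschool prevalence is only weakly stable, nothing is gained after the cost of estimating the slope.

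**No validity problem is shown.** This also stands. A reader might infer that the effect estimate is biased or the trial underpowered. Omitting the stratum does not bias the risk difference and errs on the conservative side. Chance imbalance is part of sampling error under randomisation. In the scenarios run, power for 15 points falls below 80% only at the assumed 20-point gap.

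**A baseline term may not suit every secondary outcome.** The Background describes uptake of services as low, so baseline uptake may predict little. For the primary outcome, Sample size speaks of 12-month prevalence and Data analysis of a 10-month window, so the January measure may cover a different period. A covariate need not be identical to the outcome to be useful, but the remedy for secondary outcomes should be limited accordingly.

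**Conclusion.** The point holds as a weakness in efficiency and in protection against chance imbalance. The stated primary model names neither study area nor baseline IPV, although the design stratifies on the first and collects the second in every preschool.

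Its size cannot be derived from the documents. Under the assumed persistence values and a design effect of 1.5, the gain from baseline adjustment runs from essentially nothing to a fall in the detectable difference from 13.1 to about 10.5 points. The larger gains depend on mothers' own IPV status persisting and on the same mothers answering twice. The gain from the stratum term depends wholly on how far Galle and Colombo differ: none at no gap, about three points of power at a 10-point gap, and more at 20 points. The change is worth making because it is cheap and settles the choice before data are seen, not because the planned analysis is invalid.

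**What to change.** In Data analysis, pre-specify the primary GEE with arm, study area and the preschool's January IPV prevalence as covariates, clustered on preschool. An equivalent is a two-period model of both surveys with a common baseline and preschool clustering. Say that the baseline covariate is a preschool summary, since individuals are not linked.

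For the secondary outcomes, include study area in each model, and add the preschool's baseline value where the same measure is collected in January.

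The primary covariate set should be settled in the same edit: Data analysis both adjusts the primary model for confounders and describes a confounder-adjusted analysis as a sensitivity analysis.

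Cost: no new data, and about two of 32 cluster-level degrees of freedom. If baseline prevalence proves only weakly predictive, there is little or no net gain in precision.
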